### Who will take informed consent? {26a}

Informed consent will occur for three major study activities: (1) malaria incidence follow-up, (2) product application inside homes, and (3) mosquito collections. The study will be explained in local dialects (Teso and Kiswahili), and time allocated for questions to be answered. Once all concerns are addressed, ICFs will be signed.

For consent to malaria incidence follow-up, the study will first be verbally explained to the head of compounds and HHs during which their permission will be sought to list and randomize eligible children in the compound. A single child from the master randomization list will be recruited, and an ICF will be read to the parent/guardian of the child to undergo screening for enrolment. An attempt to obtain written, informed consent from both parents of the child will be made, but consent from only one parent will be required for participation. Parent(s)/guardian(s) who cannot sign their names will provide a thumb print on the ICF for documentation of willingness to participate, and a witness not associated with the study will sign the ICF indicating the form was read, and that participation and thumb-printing were given willingly without coercion. Time will be granted to those parent(s)/guardian(s) who would wish to make consultations with their family members before signing. It will be stressed to all parents/guardians approached that their children’s entry into the study is voluntary and they may withdraw from the study at any time for any reason without any penalty. In HHs with multiple children meeting the study inclusion criteria, only one eligible child will be invited to participate. Consented subjects will be assigned a subject identity code on enrolment. Consented participants will be screened for inclusion/exclusion criteria.

For product application, all HHs within the selected clusters will be eligible to receive intervention. Informed consent from heads of HH, or spouse, will be sought for application of product in the home. Heads of HH will also be consented for mosquito light trap and HLC collections inside and/or outdoors of their homes. HH with child subjects enrolled for malaria incidence follow-up will be excluded from HLC collections. Adult males residing in consenting homes will be recruited to serve as mosquito collectors. The collectors will be asked to stay up throughout the night collecting mosquitoes that land on their exposed legs. An ICF will be obtained from the collectors.

All ICFs will include informing participants to report to a study clinic if experiencing an adverse event (AE) to be assessed and receive essential, point of care treatment free of charge whether or not the event is subsequently determined to be study related. They will only receive enough treatment to ensure they are not disadvantaged, clinically or financially, by going first to the study clinician instead of regular Ministry of Health (MOH) staff. They will not, however, receive free, comprehensive treatment for any illness found to be unrelated to study procedures (product, medicines). The ICF will also inform participants if anyone in their house becomes severely ill, they should go immediately to the nearest health facility.

Copies of informed consent documents will be made available upon request to the AEGIS Program Manager ([contact]).

### Additional consent provisions for collection and use of participant data and biological specimens {26b}

This is not applicable—participant data and biological specimens will not be used in ancillary studies.

## Interventions

### Explanation for the choice of comparators {6b}

According to the WHO VCAG’s guidelines for vector control field trial design, studies should always have a control group from which data collection occurs contemporaneously with data collection from the intervention group [34]. Our trial design includes a placebo product of matched design to the Mosquito Shield™ but with inert ingredients only. The use of a placebo is generally acceptable when a placebo is compared against an intervention in combination with standard treatment [35]. Our study design will not withhold standard-of-care for clinical management of malaria nor standard-of-care vector control interventions (e.g., LLINs, indoor residual spraying (IRS)) in either the SR or placebo arm, but instead, these will be monitored and recorded throughout the trial. This approach is aligned with WHO VCAG guidance that the control group must receive care reflecting the standard best practice interventions like routine vector control measures, such as LLINs distributed through mass campaigns, and routine health systems such as antenatal clinics or Expanded Programme on Immunization (EPI) visits. Study participants will also be encouraged to continue use of LLINs and not instructed to avoid alternative vector control tools (e.g., coils, topicals, aerosol sprays, repellents).

### Intervention description {11a}

The SR product used for the study will be a new formulation of transfluthrin, Mosquito Shield^TM^, a passive emanator that releases active ingredient over a period of up to 4 weeks. Transfluthrin is widely used in mosquito coils and other HH pest control products worldwide. The emanator consists of a pre-treated medium with a standard amount of transfluthrin that will be present throughout the treated space continuously based on a standardized 4-week replacement schedule. Products will be positioned along interior walls (approximately 2–3 m above ground) according to manufacturer specifications of 2 units per 9 m^2^. More than one emanator may be applied in a HH depending on the size of the house. A placebo product of matched design with inert ingredients will be applied similarly. Each product (SR and placebo) will have a unique code associated with an individual cluster, which will be recorded at the time of installation and replacement. Both participants and study staff will be blinded as to whether the product contains transfluthrin or is a placebo. The head of HH may be engaged about their perceptions and acceptability of the product after the product has been deployed.

### Criteria for discontinuing or modifying allocated interventions {11b}

If a participant chooses to discontinue participation in the study, study staff will respect the decision without penalty. Study staff may terminate subject participation at any time during the trial, as needed, if a subject no longer meets the inclusion criteria and/or based on AE and/or SAE clinical assessment.

### Strategies to improve adherence to interventions {11c}

In order to promote adherence to intervention, study staff will be employed to ensure the appropriate placement, quantity, and replacement schedule of products in HHs. Additionally, study staff will perform periodic, unannounced spot checks in HHs to confirm products are properly installed. If during scheduled product replacement a product has been found to have been moved after application, study teams will record for use in qualitative assessment of HH compliance. If needed, study staff will re-engage with heads of HHs to discuss importance of maintaining original product placement. Overall product coverage will be estimated based on total HHs recorded having product volume at time replacement at required levels according to manufacturer specifications (2 units/9 m^2^).

### Relevant concomitant care permitted or prohibited during the trial {11d}

Our study design will not withhold standard-of-care for clinical management of malaria nor standard-of-care vector control interventions (e.g., LLINs, IRS) in either the SR or placebo arm, but instead, these will be monitored and recorded throughout the trial. All children enrolled in the cohort will be provided a new LLIN. Study participants will be encouraged to continue use of LLINs and not instructed to avoid alternative vector control tools (e.g., coils, topicals, aerosol sprays, repellents). This will allow us to estimate the effect of the SR assuming all other measures are still occurring for malaria prevention, essentially providing insight on an additive benefit above that provided by currently recommended WHO malaria preventive measures. At baseline, children enrolled into the cohorts will be provided a treatment dose of AL free of charge according to Kenya national treatment guidelines to clear any prepatent or patent malaria parasites. Lastly, subjects will be provided treatment for malaria infection throughout the follow-up period.

### Provisions for post-trial care {30}

This is not applicable—the study will not provide post-trial care.

### Outcomes {12}

The primary outcome measure of this cRCT will be the first-time malaria incidence rate as measured by microscopy in children aged ≥ 6 months to 10 years.

Secondary outcome measures include:
Overall new *Plasmodium falciparum* malaria infections, as measured by microscopy;The first-time and overall *P. falciparum* malaria infections in buffer zones, as measured by microscopy;The first-time and overall *P. falciparum* malaria infections by two age groups (≤ 59 months old; 5 years old to 9 years and 11 months old), as measured by microscopy;Anopheline-human contact (indoor and outdoor) using human biting rate (HBR) as an indicator for all anophelines and by anopheline species, as measured by HLC during 12-h intervals on a quarterly basis;Anopheline survival and population age structure using parity rate as an indicator for all anopheline and by anopheline species, as measured by mosquito ovarian dissections from a sub-sample of anophelines collected during HLC procedures;Anopheline infectivity using sporozoite rate as an indicator for all anopheline and by anopheline species, as measured by laboratory detection of sporozoites in mosquito heads and thoraces from a sub-sample of anophelines collected during HLC and/or CDC light trap collections;Entomological inoculation rate (EIR) as an indicator of transmission intensity for all anophelines and by anopheline species, as measured by calculating the number of sporozoite-infected anopheline mosquitoes captured per person from CDC light trap and/or HLC collections;CDC light trap indoor density for all anophelines and by anopheline species, as measured by light trap collections during 12-h intervals on a monthly basis;Insecticide resistance, as measured by WHO filter paper test and CDC bottle assays during baseline and intervention phase.Adverse events (AEs) and serious adverse events (SAEs), as measured by solicited and unsolicited reports during baseline and intervention phase. Mean, minimum, and maximum frequency and percentage of AEs and SAEs across clusters among enrolled subjects will be summarized by treatment arm.

### Participant timeline {13}

The participant timeline is shown below.

**Table Tabb:** 

	Study period			
	Baseline	Intervention		Close-out
**Timepoint**	(Mar 2021–Jul 2021)	(Aug 2021–Jul 2022)	(Aug 2022–Jul 2023)	(Aug 2023–Jan 2024)
**Baseline**				
**Informed consent**	X			
**Screening**	X			
**Follow-up**	X			
**Intervention - cohort 1**				
**Allocation**		X		
**Informed consent**		X		
**Screening**		X		
**Follow-up**		X		
**Intervention - cohort 2**				
**Allocation**			X	
**Informed consent**			X	
**Screening**			X	
**Follow-up**			X	
**Assessments**				
**Baseline interim analysis**	X			
**Baseline final analysis**		X		
**Interim analysis (with intervention)**		X		
**Final analysis (with intervention)**				X

### Sample size {14}

A summary overview of sample size estimates is provided in Table 1.

Assumptions used to calculate the sample sizes below will be evaluated during the baseline phase and may lead to an adjustment in the overall sample size required for the intervention phase of the main trial. Since the adjustment will only utilize the estimated baseline incidence and coefficient of variance (CV) from the baseline without any intervention or randomization information, the type I error rate will not be inflated.

#### Primary hypothesis on first-time malaria infection

The sample size determination on the required number of subjects (HHs) per cluster for testing the primary hypothesis is based on the hazard rate comparison in the proportional hazards regression model [36, 37]. With the following specifications: 1-sided type I error rate = 5%, true PE = 30%, a between-cluster CV of hazard rate = 44% (based on historical data collected from Kenya), one interim analysis for efficacy and non-binding futility with the O’Brien-Fleming error spending function when 50% of events have been collected then 1055 first-time malaria events will need to be observed to reach 85% power in testing the primary hypothesis on PE.

With a baseline first-time malaria infection hazard rate of 3.0 per person-year, 30 clusters per treatment arm, with 20 subjects (HHs) per cluster are expected to yield 1055 independent first-time malaria events within a 12-month follow-up period per cohort post randomization to yield 85% power. If, by the end of the 2-year study, 1055 independent malaria events are not reached, the study may extend until 1055 events are collected without inflating the type I error rate in the testing of the primary hypothesis. Factoring in a LTFU rate at 35%, the required sample size is 28 subjects (HHs) per cluster, which will be split in half between the two sequential cohorts with 14 subjects (HHs) per cohort per cluster.

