### Trial design {8}

An outline of the trial design and sample size is summarized in Table 1. This study is a cluster-randomized controlled trial (cRCT) with 30 clusters per treatment arm (SR and placebo), consisting of 4 months of baseline data collection and after baseline, two independent cohorts enrolled (cohort 1 and cohort 2) and each followed for 12 months for a total of a 24-month follow-up with intervention.

**Table 1 Tab1:** Outline of the cluster design and sample size for the SR cRCT in Busia County, Kenya

Cluster design	Baseline cohort	Intervention cohorts		
	4-month follow-up (*n* = 2040)	Time of intervention deployment	12-month follow-up (cohort 1) (*n* = 2040)	12-month follow-up (cohort 2) (*n* = 2040)
**Core area** 60 clusters total	20 subjects per cluster 1200 subjects total	Year 1	SR (30 clusters), Placebo (30 clusters) 14 subjects per cluster 840 subjects total	n/a
		Year 2	n/a	SR (30 clusters), Placebo (30 clusters) 14 subjects per cluster 840 subjects total
**Buffer zone** 60 clusters total	14 subjects per cluster 840 subjects total	Year 1	SR (30 clusters), Placebo (30 clusters) 20 subjects per cluster 1200 subjects total	n/a
		Year 2	n/a	SR (30 clusters), Placebo (30 clusters) 20 subjects per cluster 1200 subjects total

For the evaluation of the primary epidemiological objective (PE), a total of 28 subjects (HHs) will be recruited from each core area of a cluster or equivalently 14 subjects (HHs) per cohort per cluster (factoring in a 35% loss-to-follow-up (LTFU) rate). For the evaluation of the secondary epidemiological objective on SR diversionary effect, a total of 40 subjects (HHs) or equivalently 20 subjects (HHs) per cohort per cluster will be recruited from each buffer zone (factoring in a 35% LTFU rate). At least one child aged ≥ 6 months old to 9 years and 11 months old from each HH will be recruited for biweekly (every 2 weeks) malaria check-ups during the follow-up period with intervention.

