#### Quantification of diversionary effect

Since there is no formal hypothesis on the SR-diversion objective, we focus on determining a practically feasible sample size that will give a relatively high precision for the estimated PE of SR in the cluster buffer zone on the malaria incidence rate. With a 44% between-cluster CV, and a baseline incidence rate of 3.0 per person-year, 30 clusters per arm with 28 subjects (HHs) per cluster leads to a half width of 0.220 for the 90% confidence interval on the log scale, or the ratio between the upper bound of the 90% confidence interval versus the point estimate is 1.245 for a hazard ratio estimate between SR and placebo buffer zone subjects (HHs). Factoring in a 35% LTFU rate, the required sample size is 40 subjects (HHs) in the buffer zone per cluster. The total subjects (HHs) will be split in half between two sequential cohorts (cohort 1 and cohort 2), with 20 subjects (HHs) per cohort per cluster.

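### The recruitment targets of 28 core and 40 buffer subjects per cluster are said to allow for 35% loss to follow-up, but cover only 28.6% and 30%

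*Protocol article*

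**What the plan says.** In Sample size {14}, under the primary hypothesis on first-time malaria infection, the plan starts from the number of subjects that gives the event target: "30 clusters per treatment arm, with 20 subjects (HHs) per cluster are expected to yield 1055 independent first-time malaria events". It then adjusts for loss: "Factoring in a LTFU rate at 35%, the required sample size is 28 subjects (HHs) per cluster". These 28 are split into 14 for each of the two intervention cohorts.

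Under Quantification of diversionary effect, the buffer zone follows the same pattern. The precision statement is "30 clusters per arm with 28 subjects (HHs) per cluster leads to a half width of 0.220 for the 90% confidence interval", and the adjustment is "Factoring in a 35% LTFU rate, the required sample size is 40 subjects (HHs) in the buffer zone per cluster", split into 20 per cohort.

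Trial design {8} repeats both targets with the same allowance: "14 subjects (HHs) per cohort per cluster (factoring in a 35% loss-to-follow-up (LTFU) rate" for the core and "a total of 40 subjects (HHs) or equivalently 20 subjects (HHs) per cohort per cluster will be recruited from each buffer zone", again with 35%, for the buffer. Table 1 carries 14 and 20 per cohort per cluster. No other rule for the loss allowance is given.

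**The concern.** In both places the plan gives the number before loss, the loss rate and the number after inflation, and the three do not agree. This is not a detail that the article leaves to a fuller document.

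The 4080 children planned for cohorts 1 and 2 (1680 core, 2400 buffer) rest on these targets. The allowance also serves as a yardstick. Trial status says that the baseline analyses are verifying loss to follow-up, among other assumptions. An observed loss of 32%, on the same time scale, would look acceptable against 35% and yet exceed what the recruitment targets cover.

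**Working it through.** **Inputs.** From Sample size {14}: 20 core subjects per cluster before loss, 28 recruited; 28 buffer subjects before loss, 40 recruited; loss 35%; 30 clusters per arm; 1055 events; hazard 3.0 per person-year; and "1-sided type I error rate = 5%, true PE = 30%, a between-cluster CV of hazard rate = 44"%. With a hazard ratio of 0.70, the hazard under the repellent is 0.70 × 3.0 = 2.1.

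**1. Is 20 the number before loss?** The Schoenfeld count for a hazard ratio of 0.70, one-sided 5% and 85% power is 227 events. The design effect for 20 per cluster is 1 + 19 × 0.44² = 4.678, and 227 × 4.678 ≈ 1062. This is close to the stated 1055, so 20 is the analysed cluster size behind the event target.

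**2. Can the stated targets be reproduced?**

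| Rule | Core, from 20 | Buffer, from 28 |
|---|---|---|
| Stated in the plan | 28 | 40 |
| n/(1 − 0.35) | 30.8 | 43.1 |
| n × 1.35 | 27.0 | 37.8 |
| n/(1 − 0.30) | 28.6 | 40.0 |

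Neither rule at 35% gives both figures. Rounding up to an even number, so that the total splits between two cohorts, gives 32 and 44 by division, or 28 and 38 by multiplication.

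**3. What loss do the targets cover?** Core: 1 − 20/28 = 28.6%. Buffer: 1 − 28/40 = 30.0%.

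**4. Who completes at 35% loss?** Core: 28 × 0.65 = 18.2 per cluster, or 1092 over 60 clusters against 1200. Buffer: 40 × 0.65 = 26 per cluster, or 1560 against 1680.

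**5. Effect on events and power if lost children contributed nothing.** At the plan's own yield, 1092 × 1055/1200 ≈ 960 events; other yield assumptions give 947 to 998. Power, ignoring the interim look, in two forms:
- Design effect: power = Φ(½√(D/DE) × |ln 0.70| − 1.645). With D = 1055 and DE = 4.678 this is 84.9%. With D = 960 and DE = 1 + 17.2 × 0.44² = 4.330 it is 84.4%. The fall is about 0.5 points.
- Variance components: Var(ln HR) = 4/D + 2 × 0.44²/30. With D = 1055 this is 0.00379 + 0.01291 = 0.01670, and power is Φ(0.3567/√0.01670 − 1.645) = 86.8%. With D = 960 it is 0.01707, and power is 86.1%. The fall is about 0.7 points. The between-cluster term is unchanged and dominates.

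**6. Events if lost children are censored when they leave.** Assume a constant dropout rate with 35% lost over 12 months: δ = −ln 0.65 = 0.431 per year. Each arm enrols 840, and expected events per arm are 840 × h/(h + δ) × (1 − exp(−(h + δ))).
- Placebo, h = 3.0: 711.
- Repellent, h = 2.1: 642.
- Total: about 1352.

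Losses spread evenly over the year give about 1370. A gamma cluster frailty with CV 44% (also an assumption) gives about 1283. All exceed 1055.

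**7. Buffer precision.** With half width = 1.645 × √(4 × DE/D), going from 28 to 26 per cluster changes it from 0.2095 to 0.2106, about 0.001. This formula does not exactly return the stated 0.220, so only the change is used.

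**The case against.** The strongest defence is that simple division suits a design in which a lost subject is discarded, and this is not one. The primary analysis is a model for interval-censored time to event, and the section on missing data keeps all available data from children who drop out for unrelated reasons. Nothing in the protocol says that 20 or 28 children per cluster must complete follow-up. On that basis step 6 shows that about 22 to 23 recruited per cluster (28 × 1055/1352 = 21.8; 28 × 1055/1283 = 23.0) would already yield 1055 events. The sample size assumptions are also to be reviewed after baseline, and the diversion objective has no formal hypothesis.

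All of this stands as an argument about consequences. It does not rescue the figures. The plan presents 28 and 40 as the result of allowing for 35%, and neither a discard rule nor a censoring rule at 35% turns 20 into 28 and 28 into 40. The section on sample size names only incidence and CV as inputs to the post-baseline adjustment, so that review does not itself correct the allowance.

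A reader might go further and infer three things that the documents do not support:
- That the event target will be missed and the study extended. This requires lost children to yield no event, which conflicts with the planned analysis, and the extension clause is optional.
- That the cause is multiplying by 1.35. That gives 27 and 37.8. A 30% allowance fits both targets better, but this too is only an inference.
- That the whole total of 6120 is affected. It includes 2040 baseline children, whose number is not derived from this calculation.

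**Conclusion.** The stated allowance is wrong as written. The targets of 28 and 40 cover 28.6% and 30% loss, not 35%, and this needs no assumption beyond the plan's own figures.

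The consequence is small. In the worst case, with lost children discarded, core completers are 9% fewer (1092 against 1200), events about 960, and power about 0.5 to 0.7 points lower. Under the planned analysis, with ignorable loss at a constant rate of 35% over 12 months, about 1350 events are expected and the target is met. The documents do not say over what period the 35% applies; 12 months per cohort is assumed here. The finding is an inconsistency to correct, not evidence of an underpowered trial, and it gives no reason to enrol more children or extend the study.

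**What to change.** Choose one of two consistent statements:
- Keep 28 and 40, and restate the loss allowance as about 28.6% for the core and 30% for the buffer.
- Keep 35%, and state that 18.2 core and 26 buffer subjects per cluster are expected to complete follow-up, together with the expected event count with children censored at loss and the dropout assumption behind it.

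Make the same change in Trial design {8} and in both parts of Sample size {14}, and use the corrected allowance as the benchmark when baseline loss to follow-up is reviewed (Trial status). The cost is a text correction. The first option shows a slightly less favourable loss allowance; neither changes the design or the recruitment numbers.
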